### Sample size and statistical analyses

According to data of two European centers (Medical University of Graz and Erasmus Medical Center in Rotterdam) and one Canadian center (Royal Alexandra Hospital in Edmonton), the percentage of neonates who survive without cerebral injury ranges from 56% to 77% and the overall percentage is 65%. Given an increase of neonates who survive without cerebral injury from 65% to 75%, 329 neonates in each group are required to detect this difference with a two-group chi-squared test with a 0.05 two-sided significance level and a power of 80%. Given a dropout rate of 10%, a total of 724 neonates will be enrolled.

Demographic and baseline data for the infants will be compared between groups (study group versus control group) using the chi-squared test or Fisher’s exact test in the case of categorical variables and using the *t* test or Mann–Whitney *U* test in the case of continuous variables. To investigate the primary hypothesis whether the frequency of cerebral injury in preterm neonates of less than 32 weeks of gestation will be different in the two groups, a chi-squared test will be performed. Secondary outcome parameters including mortality and neonatal morbidities (cerebral injury, culture-proven early-onset infection/sepsis, necrotizing enterocolitis, bronchopulmonary dysplasia, retinopathy of prematurity, and persistent ductus arteriosus receiving intervention) will be compared between groups by using the chi-squared test or Fisher’s exact test. Exploratory outcomes (need for respiratory support, intubation, and medications during resuscitation, need for mechanical ventilation and treatment with catecholamines on the first day after birth) will be compared between groups by using the chi-squared test or Fisher’s exact test; trends of monitoring parameters (SpO_2_, HR, and NIRS parameters) during the first 15 min after birth will be analyzed by using linear mixed models. With these linear mixed models, differences in the course of the monitored parameters between groups (study group versus control group) will be analyzed. Baseline characteristics, which will show significant differences between groups, will also be included in the linear mixed models.

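### Covariates for the exploratory mixed models are chosen by baseline significance tests, which costs precision and leaves the model unfixed; primary and secondary analyses are unaffected

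*Protocol article*

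**What the plan says.** All the relevant text stands in the protocol article under Sample size and statistical analyses. It first plans significance tests of baseline data between the randomised groups: "Demographic and baseline data for the infants will be compared between groups (study group versus control group) using the chi-squared test", with Fisher's exact test, the t test or the Mann–Whitney U test as alternatives. The exploratory trends in SpO2, HR and NIRS parameters "during the first 15 min after birth will be analyzed by using linear mixed models", and the stated aim is to compare their course between groups. The covariate rule closes the section: "Baseline characteristics, which will show significant differences between groups, will also be included in the linear mixed models".

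No covariate is named in advance. Three facts elsewhere in the article bear on this:

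- Under Randomization, allocation is 1:1 and stratified by trial site only.
- Under Monitoring, gestational age is among the variables recorded for each neonate.
- Under Patients, eligibility covers every gestation below 32 weeks, with no lower limit stated.

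The primary comparison does not use these models: "will be different in the two groups, a chi-squared test will be performed". The secondary outcomes are compared by chi-squared or Fisher's exact tests.

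**The concern.** In a randomised comparison, a baseline variable tests significant mostly because of the draw. The test says nothing about whether that variable predicts SpO2, HR or cerebral saturation, and prediction is the reason to adjust. The rule can therefore admit a variable unrelated to the outcome and pass over a strong predictor that happens to be balanced. Gestational age is the natural example: it is recorded for every infant, it may vary widely in this population, and it is not a stratification factor, so nothing else in the article brings it into the model. The same holds for site, although site is the stratification factor.

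At stake are the precision of the between-group comparison of oxygenation in the first 15 minutes, and whether the model can be stated before the data are seen. That comparison shows whether visible cerebral monitoring changed oxygenation at all, so it will help in interpreting the primary result whichever way it falls.

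**Working it through.** **The plan's own figure.** The article gives no figure for the covariate rule, so the sample size is reproduced as a check on inputs: "329 neonates in each group are required to detect this difference with a two-group chi-squared test with a 0.05 two-sided significance level", for 65% against 75% and 80% power. With pooled proportion 0.70:

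n = [1.960 × √(2 × 0.70 × 0.30) + 0.842 × √(0.65 × 0.35 + 0.75 × 0.25)]² / 0.10² = (1.270 + 0.542)² / 0.01 ≈ 328.5, so 329 per group.

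329 × 1.10 = 361.9, so 362 per group and 724 in total, as stated. The covariate rule does not touch this figure.

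**How often the rule admits a given variable.** Under randomisation, the probability that a baseline variable tests significant equals the level of the test. The article gives 0.05 for the primary test and no level for the baseline tests.

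- Assumed level 0.05: entry in about 5% of trials (simulated 4.8% to 5.0%).
- Assumed level 0.10: entry in about 10%.

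**Precision of the overall group difference.** Inputs are 329 per group, outcome SD 1, no treatment effect, and one baseline variable with correlation ρ to the outcome. The values of ρ are assumptions, since the article gives none. The variance of the estimated difference, in units of 2/329, is:

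- never adjusted: 1
- always adjusted: 1 − ρ²
- rule as written: (1 − ρ²) + ρ² × 0.95 × 0.759

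Here 0.759 is the variance of a standard normal variable confined to ±1.96, which is the chance imbalance left in the trials where the test is not significant. It equals 1 − 2 × 1.96 × 0.0584 / 0.95. Since √(2/329) = 0.0780, at ρ = 0.5 the rule gives 0.0780 × √(0.75 + 0.25 × 0.721) = 0.0752, and fixed adjustment gives 0.0780 × √0.75 = 0.0675. A simulation of 20,000 trials per setting agrees:

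| ρ (assumed) | SD, rule | SD, always adjusted | Variance ratio, adjusted / rule | Type I error, rule | Type I error, always adjusted |
|---|---|---|---|---|---|
| 0.3 | 0.077 | 0.075 | 0.93 | 4.8% | 5.0% |
| 0.5 | 0.075 | 0.067 | 0.80 | 4.3% | 4.9% |
| 0.7 | 0.072 | 0.056 | 0.59 | 3.6% | 4.9% |

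The ratios use unrounded SDs, for example (0.06711 / 0.07487)² = 0.80. Relative to fixed adjustment, the rule gives up about 7%, 20% and 41% of the information on the overall difference.

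**The group-by-time term.** This is a contrast within infants. A covariate that is constant over time and enters as a main effect adds the same amount to all of an infant's readings, so it cancels from that contrast. In a random-intercept simulation (300 infants, 13 time points, a strong covariate), complete data gave the same group-by-time estimate with and without the covariate, to rounding error. With 20% of readings missing at random, the largest change was 0.001 against a standard error of 0.0096, about a tenth of a standard error.

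**The case against.** The strongest reply is one of scope. The rule governs only models that the article labels exploratory, and no covariate choice can reach the primary or secondary tests. The stated interest is in the course of the monitored parameters, which is chiefly the group-by-time term, and that term hardly moves. Both points stand, and they keep this minor. The overall difference between groups in level is still estimated by the same models, and there the loss is real.

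A second reply is that the rule's wording adds covariates to terms the article does not list, and an analysis plan not shown may fix gestational age or site. This stands in part. A reader might infer that gestational age would be missing from about 95% of analyses, but the article supports only the narrower statement that this rule would bring it in about 5% of the time. The rule itself is not rescued, because it is the only covariate rule the article states.

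A third reply is that baseline differences here need not be pure chance. Infants are randomised before birth, sensor placement within 3 minutes of birth is an inclusion criterion, and consent may be deferred where local rules allow. Losses after randomisation could therefore unbalance the analysed groups. This is fair, and it is why the imbalance is called largely chance. Picking covariates by significance is no reliable cure for such losses.

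Two stronger readings are tempting and fail. One is that data-driven adjustment raises the false-positive rate; the simulated rate is below 5% at each correlation shown. The other is that the model will often be altered by luck, with 1 − 0.95^k giving 23%, 40% and 54% for k = 5, 10 and 15 variables. The article gives no number of variables, and the formula needs independence, which gestational age and birth weight would not satisfy.

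**Conclusion.** The point holds for the exploratory linear mixed models only, and it is minor. The rule selects on imbalance instead of prognosis and leaves the model unfixed until the data are seen. Its cost is precision for the overall group difference, from slight at a correlation of 0.3 to substantial at 0.7, together with slightly conservative tests (type I error 3.6% to 4.8%).

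The sizes rest on an assumed 0.05 level for the baseline tests, assumed correlations of 0.3 to 0.7, a single covariate and a single summary of the outcome per infant. The documents do not support reading this as a threat to the primary result, as inflation of false positives, or as a group-by-time result that turns on a chance draw.

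**What to change.** Replace the significance-driven sentence with a fixed list of terms for the SpO2, HR and NIRS models: group, time, group by time, site and gestational age, included whatever imbalance is observed. State that the baseline tests are not used to choose covariates. Presenting baseline data descriptively by arm, without tests, would be tidier but is optional once the tests no longer drive the model.

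The cost is wording only. Gestational age and site are already recorded or known for every infant, no new data are needed, and the sample size is unchanged. The change should be made before the outcome data are examined by group.

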### Randomization

Neonates will be randomly assigned before birth to either the study group or the control group by using the web-based randomization service (“Randomizer for Clinical Trials”), developed at the Institute for Medical Informatics, Statistics and Documentation, Medical University of Graz (https://www.randomizer.at/random/). The ratio of allocation is 1:1. Patients will be stratified according to trial site. In case of multiple births, only the first infant will be randomly assigned.

### Informed consent procedure

Parents of potential participants will be invited to enroll their preterm neonates before delivery or, if permitted by local regulations, after delivery and resuscitation (deferred consent).

### Groups

In the study group, supplemental oxygen support and respiratory/circulatory support are guided by crSO_2_ and SpO_2_/HR monitoring. In the control group, supplemental oxygen support and respiratory/circulatory support are guided by SpO_2_/HR monitoring according routine resuscitation management; the resuscitation team is blinded to the crSO_2_ monitoring.

### Duration of interventions

Monitoring and clinical interventions start within 3 min after birth and last for 15 min after birth.

### Duration of follow-up

Each neonate will be followed until discharge or until term date (37–42 weeks of gestation).

Cerebral ultrasound will be performed at 2–24 h (optional), 2–5 days, 6–8 days, 12–16 days, before discharge/37–42 weeks of gestation and MRI (optional) before discharge, or at 37–42 weeks of gestation.

### Monitoring

The antepartum medical history and birth history will be collected. Gestational age, birth weight, gender, pH of umbilical artery, and Apgar score will be documented for each neonate. Continuous positive airway pressure and positive pressure ventilation with a face mask, if necessary, will be performed.

Monitoring during the first 15 min after birth consists of (i) pulse oximetry for SpO_2_ and HR as routine non-invasive monitoring, (ii) ECG for HR as routine non-invasive monitoring, and (iii) NIRS measurements. NIRS measurements will be blinded in the control group.

For NIRS measurements, the Invos™ Cerebral/Somatic Oximeter monitor (Medtronic) with the neonatal sensor will be used.

Immediately after birth, when the neonate is brought to the resuscitation area, the cerebral NIRS sensor will be placed on the left forehead and fixed with a continuous positive airway pressure cap or elastic bandage on the left forehead. ECG electrodes will be applied to the chest for HR monitoring. One pulse-oximetry sensor will be applied to the right palm or wrist for monitoring pre-ductal SpO_2_ and HR.

### Interventions

Resuscitation will be conducted in accordance with the “Consensus Guidelines” on the management of neonatal respiratory distress syndrome [28, 29], but cerebral oxygen saturation targeting and resuscitation will be at the discretion of the clinical team.

### Control group

Depending on the infants’ breathing efforts and HR, the SpO_2_ targeting is conducted in accordance with “Local Guidelines” and “Resuscitation Guidelines” [28, 29] but at least between the 10th and 90th centiles [30] (Fig. 3). If SpO_2_ remains less than the 10th centile or below the local lower limit, respiratory support will be increased/started or fraction of inspired oxygen (FiO_2_) will be increased by 10–20% every 60 s. Respiratory support will be reduced/stopped or FiO_2_ will be reduced by 10–20% if SpO_2_ remains stable more than the 10th centile [30] or above the local lower limit for more than 60 s or if SpO_2_ is more than the 90th centile [30] or above the local upper limit. The clinical team will be blinded to the crSO_2_ monitoring.

**Fig. 3 Fig3:**
[figure not shown]
Intervention - Control group. Abbreviations: *CPAP* continuous positive airway pressure, *FiO*_*2*_ fraction of inspired oxygen, *HR* heart rate, *IPPV* intermittent positive-pressure ventilation, *SpO*_*2*_ arterial oxygen saturation

### Study group

In the study group, the crSO_2_ monitoring is visible to the clinical team (Fig. 4). If SpO_2_ is within local limits and at least between the 10th and 90th centiles, the crSO_2_ value will be considered. If crSO_2_ is less than the 10th centile (Fig. 5) [31], respiratory support will be started or increased or oxygen support will be increased every 60 s by 10–20%. In case of history of volume loss and clinical signs of volume loss, an administration of intravenous fluid (10 mL/kg) can be considered [28, 29]. Respiratory support will be reduced/stopped or FiO_2_ will be reduced by 10–20% if crSO_2_ remains stable more than the 10th centile [31] for more than 60 s or if crSO_2_ is more than the 90th centile [31].

**Fig. 4 Fig4:**
[figure not shown]
Intervention - Study group. Abbreviations: *CPAP* continuous positive airway pressure, *FiO*_*2*_ fraction of inspired oxygen, *HR* heart rate, *IPPV* intermittent positive-pressure ventilation, *SpO*_*2*_ arterial oxygen saturation

**Fig. 5 Fig5:**
[figure not shown]
10th and 90th centiles of cerebral tissue oxygen saturation (crSO_2_) in each minute after birth (according to Table 1 “All neonates” published in Pichler et al. [31])

### Outcome measure

The primary outcome measure is survival without cerebral injury defined as any grade of IVH or cystic PVL*.* The secondary outcome measures include mortality and neonatal morbidities (cerebral injury, culture-proven early-onset infection/sepsis, necrotizing enterocolitis, bronchopulmonary dysplasia, retinopathy of prematurity, and persistent ductus arteriosus receiving intervention)*.* The exploratory outcome measures are need for respiratory support, intubation, and medications during resuscitation; need for mechanical ventilation and treatment with catecholamines on the first day after birth; and monitoring parameters (SpO_2_, HR, and NIRS parameters) during the first 15 min after birth.

### Outcome assessment tools

All-cause mortality will be recorded. Cerebral injury will be assessed by cerebral ultrasound at 2–24 h (optional), 2–5 days, 6–8 days, 12–16 days, before discharge/37–42 weeks and optionally cerebral injury will be assessed by cerebral MRI, if performed routinely—mainly without sedation during postprandial sleep—before discharge or term age (37–42 weeks of gestation). Case history will be assessed until discharge or term age, depending on what comes first.

### Data management

Source data will be registered in the participant’s medical records/case report form (CRF) and the electronic CRF (eCRF). A common web-based eCRF will be used and entered in a central database (Medical Informatics, Statistics and Documentation, Medical University of Graz). Data entry into the central database is the responsibility of the investigators. After establishment of a “clean file”, the database will be locked, and data will be stored for statistical analysis at the Institute for Medical Informatics, Statistics and Documentation, Medical University of Graz.

Trial data will be handled in accordance with regulations of the data protection agency in the respective countries. After completion of statistical data analysis, data will be pseudo-anonymized and deposited at the Medical University of Graz. After the end of trial, the data will be archived for 15 years in accordance with GCP guidelines. At each trial site, the data flow will be monitored in accordance with the GCP principles by a locally appointed external monitoring committee.

### Safety

The preterm patient population is a very vulnerable and often seriously ill group. Most adverse events may be of a serious nature with or without the COSGOD trial intervention, and both groups are expected to have a very high proportion of serious adverse events (SAEs). It is therefore not possible, or meaningful, to record and report all adverse events. The SAE to be reported is mortality. Serious adverse reaction and suspected unexpected serious adverse reactions (SUSARs) will be reported to ethic committees and authorities.

An independent safety committee will perform a first monitoring after the inclusion of 20% of the neonates to evaluate the risk of SAEs and efficacy (primary and secondary outcome parameters) of the intervention with “certain” or “probably/likely” relationship with the cerebral NIRS oximeter or the application of the treatment guideline. The participants will be insured in accordance with existing legislation of their respective country.

### Ethical considerations

The COSGOD trial will start at the different centers randomly assigning participants after approvals from the relevant ethics committees and authorities have been received. All parents will receive written and oral information about the trial before they are asked for their written consent. They will enroll their newborn infant in the trial only by their own free will and can withdraw their consent for participation at any time. If a parent wishes to withdraw the consent for participation, the patient will receive treatment in accordance with the respective hospital’s standard procedures. The trial will be conducted in compliance with the guidelines of the Declaration of Helsinki in its latest form and the ICH GCP guidelines.

In case of modifications in the study protocol that are not merely of a formal nature but contain changes pertinent to the study participants, a renewed vote of the ethics committee will be obtained. If applicable, the patients/parents will be informed in the patient information and consent form about changes in the terms and conditions of the trial.

## Discussion

The primary aim of the present clinical trial is to increase survival without cerebral injury in preterm neonates by monitoring crSO_2_ in addition to routine monitoring of SpO_2_ and HR to guide supplemental oxygen delivery, respiratory support, or circulatory support (fluid bolus) (or a combination of these) in preterm neonates during the first 15 min after birth. In the pilot study [23], we demonstrated feasibility of NIRS measurements even in extremely-low-birth-weight infants. Burden of cerebral hypoxia was reduced without any SUSARs; in addition, a trend toward reduction of cerebral injury was observed. The SafeBoosC phase II randomized clinical trial recently demonstrated that the combination of crSO_2_ measurement and a treatment guideline could reduce the burden of cerebral hypoxia in preterm neonates with less than 28 weeks of gestation during the first three days after birth [32]. In this study, a trend toward reduction of cerebral injury was also observed. Both, COSGOD phase I/II and SafeBoosC phase II had trends to lower mortality or cerebral injury (or both), suggesting a positive effect on short-term outcome; however, neither study was powered for cerebral injury [23, 32].

Since pulse oximetry and ECG are recommended during immediate transition and resuscitation when monitoring is performed [28, 29], both monitoring methods will be performed in all neonates. SpO_2_ will be kept within recommended/local limits in all neonates (at least between the 10th and 90th centiles of published reference ranges) [30]. Therefore, in the study group and in the control group, hypoxia defined as SpO_2_ below the lower limit and hyperoxia defined as SpO_2_ above the upper limit should be avoided.

Monitoring of crSO_2_ would suggest increased respiratory support and increased use of supplemental oxygen in case of low cerebral oxygenation. In the COSGOD phase I/II trial, the supplemental oxygen support was lower in the NIRS-visible group in the first minutes [23]. For COSGOD III, according to ICH GCP, the research and clinical team involved in conducting this trial should be qualified by education, training, and experience to perform NIRS measurements and interventions.

Owing to the short intervention period, irritation of the skin caused by NIRS sensors will be unlikely. Moreover, this has not been observed in other studies using NIRS during immediate transition [2, 11]. Risks related to the manipulation of the patient during positioning and re-positioning of the NIRS sensors will be minimized by experience in use of NIRS. Neonates will always be continuously monitored and observed by the resuscitation team.

In conclusion, additional monitoring of crSO_2_ and dedicated interventions are feasible during immediate transition and resuscitation and reduce the burden of cerebral hypoxia. The present trial will examine whether monitoring of crSO_2_ and dedicated interventions will improve survival without cerebral injury.

## Trial status

Recruitment started in September 2018 and is expected to be completed at the end of 2020.

## Abbreviations

CBF: Cerebral blood flow
CRF: Case report form
crSO_2_: Cerebral tissue oxygen saturation
ECG: Electrocardiogram
eCRF: Electronic case report form
FiO_2_: Fraction of inspired oxygen
GCP: Good Clinical Practice
HR: Heart rate
IVH: Intra-ventricular hemorrhage
MRI: Magnetic resonance imaging
NIRS: Near-infrared spectroscopy
PVL: Periventricular leukomalacia
SAE: Serious adverse event
SpO_2_: Arterial oxygen saturation
SUSAR: Suspected unexpected serious adverse reaction
